### Randomisation and blinding

Randomisation will be based on a list of random numbers generated by a computer in a 1:1 ratio. Concealed randomisation will take place immediately after the second visit to the physiotherapist. Blinding of practitioners, children and outcome assessor is impossible. However, the investigator and parents are blinded for the web-based and PPT baseline measurements and the diary data.

### Data analysis

After checking for missing data and testing for normality, group differences will be analysed using the Pearson Chi-square test, or likelihood ratio in the case of dichotomous outcomes. Continuous outcomes will be analysed using the independent samples t-test or the Mann–Whitney U test. Adjusted group differences will be analysed using multivariable logistic regression with ordinal variables transformed into dummies, taking into account possible differences in mean number of sessions. Finally, subgroup analyses will be done to establish normal values and observed differences in effectiveness for relevant clinical subgroups.

Data analysis will be done according to the intention-to-treat principle. Characteristics of the study population at baseline will be described. Potential effect modifiers like age and gender [10,14], as well as potential confounders like urinary incontinence, enuresis and abdominal pain will be taken into account [17,47-51]. To assess selection bias, responders and nonresponders will be compared in terms of relevant clinical and demographic variables. Data analysis will be carried out using SPSS version 19.0 (SPSS Inc., Chicago, Illinois). A two-tailed p-value of 0.05 will be considered statistically significant.

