### Measurement and timing

Web-based measurements will be obtained before the first visit to the physiotherapist (M-WB 1), three months after randomisation (M-WB 2) and before the final visit to the physiotherapist (M-WB-3) (Figure 1). Shortly before randomisation (M-PPT 1) and at six month, adjacent to M-WB 3, measurements at the physiotherapist will take place (M-PPT 2). After M-PPT 2 a final visit at the paediatrician is scheduled.

Web-based measurements include a structured patient reported outcome, which assesses the presence of the Rome III criteria and laxative use, co morbidity (such as urinary problems and abdominal pain), the Strength and Difficulties Questionnaire (SDQ), the numeric rating scale (with regard to experienced burden) and a two weeks diary. At follow-up (M-WB 2 and M-WB 3) the web-based measurements are supplemented with the global perceived effect (GPE).

At the last visit at the paediatrician, use of laxatives and the presence of Rome-III-criteria (primary outcome) are recorded.

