#### Primary outcome measure

The primary outcome measure is the absence of FC according to the Rome III criteria. The use of less than 10 g of macrogol 3350 or 4000 a day, as a maintenance dose, is allowed.

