### Power of the study

The sample size of this study has been calculated on the basis of a clinical difference of minimal relevance in terms of proportions. The success rate (absence of FC) of the controls has been set at 60% [30,44-46]. There is no published PPT success rate but it is estimated to be 75%. Based on a two-sided effect, an alpha of 0.05, a power of 80% and an expected drop-out rate of 20%, at least 367 children should be enrolled in this study.

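### No stated analysis of the binary primary outcome adjusts only for baseline predictors, and none is named primary, so precision available from M-WB 1 data may go unused

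*Protocol article*

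**What the plan says.** The Primary outcome measure section fixes a binary endpoint: "The primary outcome measure is the absence of FC according to the Rome III criteria", with a limited daily laxative maintenance dose permitted.

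For such outcomes the Data analysis section states that "group differences will be analysed using the Pearson Chi-square test, or likelihood ratio in the case of dichotomous outcomes". Neither test uses covariates. The same paragraph then plans adjusted group differences by multivariable logistic regression, allowing for differences between arms in mean number of sessions. The Discussion links this to unequal numbers of protocolised contacts. Neither analysis is labelled primary.

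Covariates are given by example. Age and gender appear as effect modifiers, and "potential confounders like urinary incontinence, enuresis and abdominal pain will be taken into account". The Discussion adds laxative use, without saying whether baseline or on-treatment use is meant.

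On data collection, the Measurement and timing section says "Web-based measurements will be obtained before the first visit to the physiotherapist (M-WB 1"). The web-based instrument "assesses the presence of the Rome III criteria and laxative use, co morbidity", and it also contains the NRS of experienced burden. Randomisation follows the second physiotherapist visit (Randomisation and blinding), so everything in M-WB 1 precedes allocation.

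**The concern.** In a randomised trial the main statistical reason to adjust is that a baseline variable predicts the outcome. Adjusting for such variables reduces the variance of the treatment comparison and removes the effect of chance imbalance in them. Here the plan collects, before allocation, the baseline counterparts of both parts of the endpoint: the Rome III items and laxative use. All children meet at least two of the six criteria at entry, so the diagnosis is constant, but the number of criteria met can run from 2 to 6. A rating of burden is collected as well.

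The two stated analyses leave a gap between them. The unadjusted test cannot use these data. The logistic model could, but it also takes sessions into account. Number of sessions arises after randomisation and is part of how the arms differ, so that model does not estimate the plain effect of assignment. The covariates are framed as confounders, and the Discussion's reason for incontinence, enuresis and pain is their influence on perceived quality of life and on the SDQ and GPE scores, not on absence of constipation.

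At stake is some power and a narrower interval for the risk difference, obtainable from data already planned.

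**Working it through.** **Inputs.** From Power of the study: control success 60%, experimental success 75%, two-sided alpha 0.05, power 80%, drop-out 20%, total 367. From Randomisation and blinding: 1:1 allocation. Not in the document: rho, the correlation between the baseline covariate set and the outcome. It is assumed, from 0 to 0.4.

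**Step 1: the plan's own figure.** The pooled proportion is (0.60 + 0.75)/2 = 0.675. The variance terms are 2 × 0.675 × 0.325 = 0.43875 under the null and 0.60 × 0.40 + 0.75 × 0.25 = 0.4275 under the alternative.

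n per arm = (1.96 × √0.43875 + 0.8416 × √0.4275)² / 0.15² = 151.9, so 152 per arm and 304 in total.

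- 304 × 1.2 = 365, close to 367.
- 304 / 0.8 = 380.
- With unpooled variance, 150 per arm: 300 / 0.8 = 375.

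The stated 367 therefore comes from an unadjusted two-proportion calculation and assumes no gain from covariates.

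**Step 2: unadjusted power after the allowed drop-out.** 367 × 0.8 = 293.6, about 147 per arm. SE under the null = √(0.43875/147) = 0.0546; under the alternative √(0.4275/147) = 0.0539.

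Power = Φ((0.15 − 1.96 × 0.0546)/0.0539) = Φ(0.796) = 78.7%.

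**Step 3: power with baseline adjustment.** Both standard errors are multiplied by √(1 − rho²).

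| rho (assumed) | SE multiplier | Power |
|---|---|---|
| 0 | 1.000 | 78.7% |
| 0.2 | 0.980 | 80.3% |
| 0.3 | 0.954 | 82.4% |
| 0.4 | 0.917 | 85.3% |

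**Step 4: check by simulation.** 294 children, 2,000 trials per setting, one normally distributed prognostic score, marginal success rates held at 60% and 75%. R² is the share of control-arm outcome variance explained by the score, so rho = √R².

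| R² (rho) | Chi-square power | Adjusted logistic power | SD of risk difference, unadjusted → standardised | SE of log odds ratio, unadjusted → adjusted |
|---|---|---|---|---|
| 0 (0) | 79.0% | 78.9% | 0.0551 → 0.0552 | 0.256 → 0.257 |
| 0.054 (0.23) | 79.4% | 80.6% | 0.0548 → 0.0537 | 0.256 → 0.264 |
| 0.17 (0.41) | 79.9% | 86.4% | 0.0540 → 0.0493 | 0.256 → 0.283 |

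The Monte Carlo standard error is about √(0.8 × 0.2/2000) = 0.9 percentage points, so the simulation agrees with the formula. The last column matters for reporting. Adjustment raises power and tightens the standardised risk difference, but it does not narrow the interval for the log odds ratio, because the adjusted odds ratio is a different, conditional quantity.

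**The case against.** The case against is substantial, and most of it stands.

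- **The chi-square test is valid.** It also matches the two-proportion basis of the sample size. A reader might infer that the primary comparison is wrong or biased; the document does not support that. Chance imbalance does not bias a randomised comparison, and the test's error rate already allows for it.
- **The chi-square test is not named as primary.** Treating it as the headline result is an inference from its coming first and matching the sample size.
- **The covariate list is open.** It is introduced by example, so failing to name Rome III items and NRS does not exclude them. Age and laxative use are already mentioned. A closed list may sit in a full protocol or SAP that is not shown, and its absence from an article is not a fault.
- **Some proposed covariates need care.** No Rome III severity score is defined, although a count follows from the items. M-WB 1 is said to record laxative use; dose is not mentioned.
- **The gain is unknown.** Nothing in the article shows how well these variables predict the outcome. A reader might assume a strong correlation such as 0.5 and quote a large gain, but no figure in the document supports that.
- **Drop-out is provided for.** A reader might take 78.7% to mean that the design has no reserve. The 367 already includes a 20% allowance, and 78.7% is the power after that loss, 1.3 points short of target.

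What survives rests on stated text. One stated analysis has no covariates. The other takes a post-randomisation variable into account. The section does not rank them.

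**Conclusion.** The point holds as a recommendation on efficiency and clarity, not as an error or contradiction. As written, no analysis of absence of functional constipation adjusts solely for pre-randomisation predictors, and the primary analysis is not identified.

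Baseline adjustment would move power by roughly 2, 4 or 7 percentage points at rho 0.2, 0.3 or 0.4 (78.7% to 80.3%, 82.4% or 85.3%), and by nothing near rho 0. This rests on the plan's 60% and 75%, on the full 20% drop-out occurring, and on an assumed rho. The simulation also assumes a single, correctly modelled score, so a 2-to-6 count and a 1–10 rating may do less well.

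**What to change.** In the Data analysis section, name one primary analysis of absence of functional constipation: logistic regression on randomised arm with a short covariate set fixed in advance, all from before randomisation:

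- number of Rome III criteria met at M-WB 1;
- laxative use at M-WB 1 (dose, if it is recorded);
- parent NRS at M-WB 1;
- age.

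Leave number of sessions and on-treatment laxative use out of this model. Report the result as a standardised (marginal) risk difference with 95% CI, so that it answers the same 60% versus 75% question as the sample size. Keep the Pearson chi-square test as the supportive unadjusted analysis.

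The cost is a change of wording, with no new data if laxative use rather than dose is the covariate, and no change in sample size. The small downside is that the primary result becomes model-based instead of being read from a 2×2 table, and the covariates must be fixed before the data are seen.

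### SDQ and NRS have a pre-randomisation value, but the only tests named for continuous outcomes do not adjust for it: a minor loss of precision on secondary outcomes

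*Protocol article*

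**What the plan says.** **Analysis.** The Data analysis section puts a check of normality before the group comparisons. It then says: "Continuous outcomes will be analysed using the independent samples t-test", with the Mann–Whitney U test as the alternative. The only adjusted model it names is multivariable logistic regression. The covariates it names are age and gender as effect modifiers, and urinary incontinence, enuresis and abdominal pain as confounders; it also mentions the number of sessions. No baseline outcome value is on the list.

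**Data.** According to Measurement and timing, each web-based measurement includes "the Strength and Difficulties Questionnaire (SDQ), the numeric rating scale (with regard to experienced burden") and a diary. The first of these, M-WB 1, precedes the first physiotherapist visit. Randomisation and blinding places randomisation directly after the second visit, so the first SDQ and NRS values are true baselines. Both scores are taken again at 3 months and before the final visit at about 6 months. GPE is asked only at follow-up.

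**Intent.** Under Trial design, SDQ, NRS and GPE carry the first secondary question, which is about treatment effect. The Discussion says that adjusted group differences will be analysed, and that incontinence, enuresis and pain could distort SDQ and GPE scores.

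**The concern.** A score taken before randomisation and again afterwards usually correlates with itself. Using the first value as a covariate removes that shared variation from the treatment comparison without collecting anything new. As written, the plan names no method for a continuous score that does this.

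There is also a mismatch between aim and tool. The Discussion wants adjusted results and mentions SDQ in that context, but a logistic model gives an adjusted effect on a 0–40 or 1–10 score only if the score is cut in two, and no cut for that purpose is stated.

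Finally, letting a normality test decide between the t-test and Mann–Whitney makes the reported quantity (a mean difference or a rank comparison) depend on the data. At stake are wider intervals and lower power on the first secondary question, and an effect measure not known in advance.

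**Working it through.** **1. The plan's own figure.** The article gives a sample size only for the binary primary outcome. Inputs from Power of the study: "The success rate (absence of FC) of the controls has been set at 60" per cent; "There is no published PPT success rate but it is estimated to be 75" per cent; "Based on a two-sided effect, an alpha of 0.05, a power of 80% and an expected drop-out rate of 20" per cent. Allocation is "generated by a computer in a 1:1 ratio". The Data analysis section confirms the two-sided level: "A two-tailed p-value of 0.05 will be considered statistically significant".

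Pooled formula for two proportions, mean proportion 0.675:

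n per arm = [1.960·√(2·0.675·0.325) + 0.842·√(0.60·0.40 + 0.75·0.25)]² / 0.15² ≈ 152

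- Multiplied up: 2 × 152 × 1.2 ≈ 365. With 153 per arm, 2 × 153 × 1.2 = 367.2.
- Unpooled variance: 150 per arm, and 300/0.8 = 375.
- Pooled and divided by 0.8: 304/0.8 = 380.

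The stated figure ("at least 367 children should be enrolled in this study") is therefore closely reproduced. It does not rest on SDQ or NRS, so nothing below changes it.

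**2. Completers.** 367 × 0.8 / 2 = 146.8 per arm.

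**3. Variance factors.** Let r be the baseline-to-follow-up correlation and assume equal variances at the two times. Relative to the variance of a follow-up value:

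- follow-up value alone: 1
- change score: 2(1 − r)
- ANCOVA: 1 − r²
- so ANCOVA relative to change score: (1 − r²) / [2(1 − r)] = (1 + r)/2

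The documents do not give r; the values below are assumed.

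| r | ANCOVA vs follow-up value | equivalent extra children | ANCOVA vs change score | equivalent extra children |
|---|---|---|---|---|
| 0.3 | 0.91 | 10% | 0.65 | 54% |
| 0.5 | 0.75 | 33% | 0.75 | 33% |
| 0.7 | 0.51 | 96% | 0.85 | 18% |

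Extra children = 1/factor − 1. Below r = 0.5 a change score is noisier than the follow-up value alone (2 × 0.7 = 1.4 at r = 0.3).

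**4. Power, if follow-up values are compared.** The unadjusted t-test has 80% power for (1.960 + 0.842)·√(2/146.8) = 0.327 SD. Multiplying by √(1 − r²), the detectable difference under ANCOVA is 0.312, 0.283 and 0.234 SD at r = 0.3, 0.5 and 0.7. For the same 0.327 SD, ANCOVA power is 83.6%, 89.9% and 97.5%.

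**5. Does choosing by a normality test do harm?** Simulation with 147 per arm, 4,000 runs per setting, and normal or lognormal outcomes (log-scale SD 0.5, r set on the normal scale):

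- With no effect, the pre-test procedure rejected in 4.9% to 5.9% of runs (Monte Carlo error about 0.35 points). Type I error is essentially intact.
- Normal data, effect 0.327 SD: pre-test procedure 80%; ANCOVA 89% (r = 0.5) and 98% (r = 0.7).
- Lognormal data: Mann–Whitney 93% against 87% for untransformed ANCOVA at r = 0.5, and 94% against 96% at r = 0.7.

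**6. What the pre-test would do to NRS.** Whole-number 1–10 scores were simulated as rounded normal values for 147 children, with assumed means of 3 to 5.5 and SDs of 1.5 to 2.5. Shapiro–Wilk and Lilliefors rejected normality in every run, because the scale is discrete. If the pre-test decides, NRS would go to Mann–Whitney almost automatically.

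**The case against.** **The tests are valid, and a rank test can be the better one.** This stands. Randomisation makes the unadjusted comparison unbiased on average, and the simulation shows no material inflation of type I error. A reader might infer that the named tests waste precision for nothing in return. The lognormal result contradicts that: under marked skew Mann–Whitney can beat an untransformed linear model. A shift estimate in scale points can also accompany it.

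**The article does not say whether follow-up values or changes are tested.** This stands too. It would be tempting to say that no continuous outcome uses its own baseline and to quote 96% more children at r = 0.7. That holds only for follow-up values; against change scores the figure at r = 0.7 is about 18%.

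**Pelvic floor function.** A reader might extend the point to all pelvic-floor outcomes. The documents do not support that. The stated question there is which values can be defined in subgroups, which is descriptive. Digital testing, reflex reactions and the normal/abnormal ratings are categorical. Only EMG levels and balloon volumes, if compared between arms, fall under this point.

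**The correlation is unknown.** True. Excluding children with an SDQ of 14 or more narrows the baseline range and may lower r for that score.

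**This is detail for the analysis plan.** Only partly. Covariates for secondary models are often left to that document, and their absence from an article would not be a finding. Here, however, the article itself fixes the tests, puts a normality check before them, and names an adjusted model that does not fit the scores it wants adjusted.

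**Conclusion.** The point holds as a minor one, for SDQ and NRS. The article commits to tests without baseline adjustment for scores whose baseline is already collected, and the only adjusted model it names cannot serve them. The cost is precision, not validity: a variance factor of 0.91 to 0.51 in favour of ANCOVA if follow-up values are compared, or 0.65 to 0.85 if change scores are, for r from 0.3 to 0.7. These figures rest on an assumed r, equal variances at the two times, a linear relation and about 147 completers per arm. Under strong skew the advantage over a rank test can shrink or reverse. The primary outcome, its analysis and the sample size are not touched.

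**What to change.** State in the analysis plan, before any outcome is compared by arm:

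1. SDQ and NRS, and any EMG level or balloon volume that is compared between arms, are analysed by a linear model on arm with the baseline value of the same measure as covariate. Where both the 3- and 6-month values exist, one repeated-measures model with baseline as covariate is an alternative. Confounders already intended for adjustment can enter the same model.
2. The result is reported as an adjusted mean difference with 95% CI.
3. No normality test selects the method. Use robust or bootstrap standard errors, and keep a rank-based or transformed analysis as a sensitivity check.
4. GPE has no baseline and keeps a two-group comparison.

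The cost is a few sentences of analysis wording. No visit, measurement or child is added.

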### Framework of the study

A child’s participation to the study starts and ends with a visit to a paediatrician. In our multicentre randomised controlled trial, the control group will receive only standard medical care (SMC) (Figure 1) whereas the experimental group will have SMC supplemented with PPT (Figure 2). The control group will have at least three contacts with the paediatrician in five months while the experimental group will have a maximum of six contacts with the physiotherapist. The study duration will be six months from randomisation, with a three-year recruitment period.

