## Discussion

Why publish a study protocol? This study aims to show that pelvic physiotherapy in combination with standard medical care is more effective than standard medical care alone in constipated children. To our knowledge, this article is the first to describe the design of an RCT among children with FC to assess the effect of PPT as an add-on to SMC. The Dutch Pelvic Physiotherapy Protocol (DPPP) presented here is based on the available literature, a survey and a Delphi procedure among experts. Exchanging knowledge and expertise with other researchers is important in order to prevent duplicate research. Consequently, it has been decided to publish the study protocol prior to achieving results.

The DPPP was developed between 2007 and 2009. Given that no studies have so far been published on the effect of PPT in childhood constipation [52] and that a repeat survey on standard PPT among 49 Dutch physiotherapists in 2011 did not yield substantial differences compared to the 2007 survey, we feel this protocol is as up-to-date as possible.

In the absence of an evaluation tool, we will use parameters for male adults to define the proper childhood pelvic floor muscle functions. These values are expected to be similar to the children’s, as is also the opinion of the experts and the literature [36].

Confounding in our trial may arise due to the Hawthorne-effect as a result of differences in number of the protocolised contacts. Although it is expected, based on experience, that the mean number of treatment sessions will be equal, adjusted group differences will be analysed.

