Patients' compliance with the home toilet training and the use of laxatives will be monitored, as it determines the therapy intensity and, indirectly, the success of the therapy. Finally, the use of laxatives will be taken into account, as it can influence the number of stool events and consistency. The results of this trial will be used to evaluate the proposed Dutch pelvic physiotherapy protocol and to determine normal values for the pelvic floor muscle function in children. These outcomes will serve as recommendations in the guideline on PPT in constipated children, which will be developed using the standard method for clinical practice guideline development of the Royal Dutch Society for Physical Therapy (KNGF).

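### The adjusted group difference controls for number of sessions, which arises after randomisation and carries the treatment, so it is not the declared intention-to-treat effect

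*Protocol article*

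**What the plan says.** The Data analysis section first plans an unadjusted comparison of dichotomous outcomes (Pearson chi-square or likelihood ratio). It then plans adjusted group differences from "multivariable logistic regression with ordinal variables transformed into dummies, taking into account possible differences in mean number of sessions". The same section declares an intention-to-treat analysis. It does not say whether the unadjusted or the adjusted estimate is primary.

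The Discussion gives the reason. It treats unequal numbers of protocol contacts as a source of confounding through a Hawthorne effect, and continues: "Although it is expected, based on experience, that the mean number of treatment sessions will be equal, adjusted group differences will be analysed".

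Under Framework of the study the contacts are set by arm: the control group has "at least three contacts with the paediatrician in five months while the experimental group will have a maximum of six contacts", the latter with the physiotherapist. Under Randomisation and blinding, allocation follows directly after the second physiotherapist visit.

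On laxatives, the Discussion lists their use among potential confounders without a time point. In a paragraph on monitoring during the trial it adds: "Finally, the use of laxatives will be taken into account, as it can influence the number of stool events and consistency".

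**The concern.** A confounder of a treatment comparison must influence both who gets the treatment and the outcome. Randomisation removes such variables, apart from chance imbalance at baseline. Number of sessions is not of this kind, because allocation comes first and sessions follow from it. Conditioning on it can do two kinds of harm:

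- If sessions are how the physiotherapy works, holding them constant takes part or all of the benefit out of the estimated effect.
- If sessions also track prognosis, comparing children with equal session counts compares children who differ in severity between arms. The benefit of randomisation is lost, and a difference can appear where there is none.

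The hypothesis is that standard care plus pelvic physiotherapy is better than standard care alone. A session-adjusted odds ratio does not answer that question. Since no estimate is named as primary, it could still become the headline result.

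**Working it through.** **1. Order of events and source of the variable**

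| Step | Where stated | Consequence |
|---|---|---|
| Allocation follows the second physiotherapist visit | Randomisation and blinding | Treatment sessions are counted after allocation |
| Minimum of three paediatrician contacts against maximum of six physiotherapist contacts | Framework of the study | The count depends on arm by design |
| Intensity tailored to age, motivation of child and parents, co-morbidity and cognition | The Dutch pelvic physiotherapy protocol | The count may also carry prognosis |
| Session number enters the adjusted model | Data analysis; Discussion | The model conditions on a consequence of allocation |

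**2. Target effect from the plan's own figures**

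Power of the study assumes success of 60% in controls and 75% with physiotherapy. The intention-to-treat odds ratio (OR) is (0.75/0.25)/(0.60/0.40) = 3.0/1.5 = 2.0. With 20% drop-out, 367 × 0.8 = 293.6, so about 294 children are analysed.

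**3. What session adjustment does to that effect**

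The article gives no session distributions, so those below are assumptions. ORs come from logistic regression of success on arm, with and without sessions, in 400,000 simulated children. Type I error comes from 2,000 simulated trials of 294.

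*Case A: sessions carry the effect, with no link to prognosis.* Control sessions are 3 + Binomial(3, 0.15), mean 3 + 0.45 = 3.45. Experimental sessions are 3 + Binomial(3, 0.7), mean 3 + 2.1 = 5.1. The mediated share of the total log OR (ln 2 = 0.693) is spread over the mean difference of 1.65 sessions; the rest acts directly through arm.

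| Share through sessions | Unadjusted OR | Session-adjusted OR |
|---|---|---|
| 0% | 1.99 | 1.98 |
| 50% | 1.99 | 1.42 |
| 100% | 1.94 | 0.99 |

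*Case B: sicker children get more sessions.* Severity u is standard normal and logit P(success) = a − u, with a set to give 60% and 75% overall (60% in both arms under the null). Control sessions are 3 + Poisson(0.5·exp(0.3u)). Experimental sessions are 5 + 0.7u plus normal noise (SD 0.8), rounded and held between 1 and 6. The means are 3.5 and 4.9.

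| Truth | Unadjusted OR | Session-adjusted OR |
|---|---|---|
| 60% vs 75% | 2.01 | 3.70 |
| No effect | 1.00 | 1.86 |

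Under the null, type I error is 0.48 with sessions in the model and 0.05 without. A separate simulation, with other assumed parameters and means of 3.5 and 5, gave a null OR of 2.4.

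*Case C: means nearly equal (3.8 vs 4.0), severity-driven, but different distributions by arm.* The null OR is 1.09 and type I error is 0.071, against 0.055 unadjusted.

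*Case D: the same session distribution in both arms.* If sessions are unrelated to outcome, the adjusted OR is 2.01 with a true effect and 1.00 under the null. If sessions are severity-driven, the null OR stays at about 1.0, while the OR under a true effect rises to between 2.13 and 2.45 depending on parameters. That rise is non-collapsibility of the odds ratio (a conditional OR lies further from 1 than the marginal OR), not bias.

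The null rows are therefore the clean evidence of bias in the severity-driven cases. The 3.70 in Case B mixes bias with some non-collapsibility.

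**The case against.** The strongest defence has three parts. The unadjusted test is planned, is named first and is unaffected by sessions. Equal mean sessions are expected. And separating an attention effect from the effect of physiotherapy is a legitimate question.

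The first part stands, and limits the point to the adjusted model. The second stands in part: with the same distribution in both arms there is no bias under the null. But equality is only expected from experience, and the adjustment is planned regardless. The third stands as a secondary aim. Adding sessions as a covariate does not isolate attention, however: a direct effect needs assumptions about common causes of sessions and outcome, and the article states none.

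A reader might infer more than the article supports:

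- *That the trial cannot show a benefit.* The chi-square comparison can.
- *That in-trial laxative use is in the model.* The confounders named under Data analysis do not include laxatives, and the Discussion gives no time point. Use is also recorded at the first web-based measurement (M-WB 1), so a baseline covariate is an open reading, although the monitoring context leans towards in-trial use.
- *That compliance is adjusted for.* It is only monitored.
- *That sessions follow the child's response.* Response is not among the listed reasons for tailoring, and session number is not named there. The link to severity in Case B is an assumption, though co-morbidity could supply it.
- *That equal means contradict the schedules.* A minimum of three and a maximum of six overlap; means of 4 in both arms satisfy both.

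**Conclusion.** The session adjustment is wrong as written. It is explicit in two places, treats a consequence of allocation as a confounder, and yields an odds ratio that is not the declared intention-to-treat effect. That conclusion needs no simulation.

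The size does. With assumed means of about 3.5 and 5 sessions, a true OR of about 2 can fall to about 1.0, or a null effect can appear as about 1.9 to 2.4. With near-equal means the distortion is small, and with identical distributions it is absent under the null. The direction cannot be predicted from the article. The unadjusted comparison is sound, but because no estimate is designated primary, the article does not secure that the sound one will carry the conclusion. On laxatives the defect is one of clarity: the article leaves open whether baseline or in-trial use is meant.

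**What to change.** 1. Remove number of sessions from every model that estimates the treatment effect.
2. Name the unadjusted or the baseline-adjusted intention-to-treat comparison as primary.
3. Restrict covariates to measurements taken before randomisation: age, sex, and baseline urinary incontinence, enuresis and abdominal pain.
4. Where laxative use is to be accounted for, state that only use at M-WB 1 enters the model. Guiding laxative use is part of the physiotherapy intervention, and a macrogol limit is part of the primary outcome definition, so in-trial use does not belong in a treatment-effect model.
5. Report contacts (paediatrician and physiotherapist) and in-trial laxative use by arm. Label any session-adjusted or attention-effect analysis exploratory and non-randomised, and state its assumptions.

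The cost is a few sentences of analysis wording. No new data are needed and the planned 367 children are unchanged.
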